## Abstract

**Background:**

Many patients at high risk of cardiovascular diseases are managed and monitored in general practice. Recommendations for cardiovascular risk management, including lifestyle change, are clearly described in the Dutch national guideline. Although lifestyle interventions, such as advice on diet, physical exercise, smoking and alcohol, have moderate, but potentially relevant effects in these patients, adherence to lifestyle advice in general practice is not optimal. The IMPALA study intends to improve adherence to lifestyle advice by involving patients in decision making on cardiovascular prevention by nurse-led clinics. The aim of this paper is to describe the design and methods of a study to evaluate an intervention aimed at involving patients in cardiovascular risk management.

**Methods:**

A cluster-randomised controlled trial in 20 general practices, 10 practices in the intervention arm and 10 in the control arm, starting on October 2005. A total of 720 patients without existing cardiovascular diseases but eligible for cardiovascular risk assessment will be recruited.

In both arms, the general practitioners and nurses will be trained to apply the national guideline for cardiovascular risk management. Nurses in the intervention arm will receive an extended training in risk assessment, risk communication, the use of a decision aid and adapted motivational interviewing. This communication technique will be used to support the shared decision-making process about risk reduction. The intervention comprises 2 consultations and 1 follow-up telephone call. The nurses in the control arm will give usual care after the risk estimation, according to the national guideline.

Primary outcome measures are self-reported adherence to lifestyle advice and drug treatment. Secondary outcome measures are the patients' perception of risk and their motivation to change their behaviour. The measurements will take place at baseline and after 12 and 52 weeks. Clinical endpoints will not be measured, but the absolute 10-year risk of cardiovascular events will be estimated for each patient from medical records at baseline and after 1 year.

**Discussion:**

The combined use of risk communication, a decision aid and motivational interviewing to enhance patient involvement in decision making is an innovative aspect of the intervention.

**Trial registration:**

Current Controlled Trials ISRCTN51556722

## Background

Despite a decreasing trend in mortality from cardiovascular diseases, these diseases are still the main cause of mortality in the Western world, and cardiovascular diseases cause 33% of all deaths in the Netherlands [1,2].

Unhealthy lifestyles, rather than medical conditions or genetic predisposition, are thought to be the most important and modifiable causes of the majority of deaths from CVD [3,4]. It is estimated that 30% of all new cases of coronary heart disease and 19% of all strokes are caused by smoking, while other lifestyle factors, such as diet, also play an important role in the development of CVD [5].

Preventive guidelines on CVD and diabetes recommend medical treatment for patients at high risk. In addition, they recommend patient education and counselling on smoking, diet, physical exercise and alcohol consumption for large groups of patients with moderately increased risk. The Dutch multi-disciplinary guidelines for cardiovascular risk management (CVRM) also underline the importance of a healthy lifestyle for the prevention of CVD. The core of the guideline consists of a risk table for the assessment of the 10-year risk of CVD, showing the various risk factors which can be reduced [6].

Lifestyle changing programmes for the prevention of CVD have shown moderate but significant effects and have proved to be cost-effective [7-12]. However, changing lifestyle is very difficult for people. The public's adherence to lifestyle advice and medication varies between 20 and 90%, with most estimates converging around 50% [13,14]. Improving this adherence requires effective interventions, comprising educational and behavioural components [15]. Adherence seems to be influenced by health beliefs such as risk perception, perceived benefits and disadvantages of treatment and self-efficacy, as well as stage of change and communication problems with physicians [16-18]. Each high-risk individual can usually choose between several options for risk reduction. Since patients seek treatment approaches which are manageable and in their view effective, their preferences can differ considerably from those of the professionals. Many people prefer lifestyle change to drug treatment, but beliefs about treatments differ between physicians and patients, making it difficult to achieve consensus about the best treatment. True dialogue is required if patients' preferences are to be used to make decisions effectively [19,20].

The IMPALA (IMproving Patient Adherence to Lifestyle Advice) project builds on earlier work at our department. [name] evaluated the effect of implementation of the Dutch cholesterol guideline for cholesterol among 6 GPs [21]. This resulted in negative findings, without improvement in underuse or overuse of statins. It appeared that the mismatch between the guideline and the patients' expectations or preferences was one of the main barriers to change. [name] tried to involve patients in the decision-making process for cardiovascular risk reduction by implementing a decision support tool and using a risk table. He found no effect on the GPs' performance and a minimal effect in terms of the patients' cardiovascular risk reduction. From process evaluation it appeared that the patients had not been optimally exposed to the decision support tool. It was recommended delegating CVRM to a practice nurse and extending the implementation for involving the patient in CVRM [22]. For the IMPALA study, an innovative nurse-led implementation strategy was developed, comprising key elements of risk assessment, risk communication, a decision aid, and adapted motivational interviewing. The IMPALA study investigates whether patients' adherence to medication and lifestyle advice can be increased through patient involvement and shared decision making [20].

Many of the patients with moderate to high CVD risk, but without existing CVD, are monitored in primary care. According to the guideline for CVRM, prevention of CVD, especially patient education and support in lifestyle change, seems to be a good task to delegate to a practice nurse in primary care [6]. The number of general practices employing a qualified practice nurse is increasing. These practice nurses mainly perform standardised tasks for patients with chronic diseases like asthma, hypertension or diabetes. The nurse works under the supervision of a general practitioner.

Most patients have difficulty understanding CVD risks [22,23]. Perception of risks tends to be inaccurate and people find it difficult to interpret and act upon risk information. The format (framing) in which risk information is presented affects people's perception of risks and their decisions. For instance, information framed in terms of relative risk or loss framing is more persuasive than framing in terms of absolute risk or gain framing. This has been reported for both doctors and patients [24-29]. Risk communication should include weighing up the risks and benefits of a treatment choice, and should address the patient's perception of the probability of an event as well as the importance of the event for that individual [26].

Increasing people's competence to understand their actual cardiovascular risk, the pros and cons of possible treatments and their options for modifying the risk, as well as the competence to clarify their own values and to become involved in the decisions, seems to lead to better-informed decisions [18,30-32]. Information on treatment options and their advantages and disadvantages is ideally integrated in a well-designed and validated decision aid [33], which can help both physicians or practice nurses and patients in the process of making the best choice for the management of CVD risk. It may help the unaware high-risk person to agree with risk-reducing strategies and the 'worried-well' low-risk person to agree with non-indication for risk-reducing drugs. There is increasing evidence that decision aids increase patients' active involvement in decision making [32]. However, assessing the 10-year risk of CVD and informing the patient about different options for risk reduction is only one step in a process of lifestyle change. Additional components are needed to reach a shared decision which the patient is motivated to adhere to. Professionals will have to facilitate the process, and to communicate in a patient-oriented way.

The motivational interviewing method seems a good tool, in addition to the use of the risk chart and the decision aid, to achieve shared decision making [32]. Adapted motivational interviewing has been used [34] to set the agenda of consultations together with patients, to assess patients' motivations for behaviour change and build motivation for healthy behaviours, and to achieve goal setting and specific action plans. Motivational interviewing is an approach that can be described by its four basic principles: expressing empathy, developing discrepancy, rolling with resistance and supporting self-efficacy [34-36]. The consultations for the IMPALA intervention will be held in the spirit of these basic principles, and an adapted form of motivational interviewing will be used. Since it is possible that the two consultations will only be the first step in a long process of preventive support, a telephone consultation is added to the intervention as the initial step towards follow-up. Telephone counselling by practice nurses seems a valuable approach for adequate follow-up support [37,38].

The impact of the IMPALA intervention will be assessed by means of various evaluations. First, the effect of the nurse-led intervention on the adherence to lifestyle advice will be examined and compared with that of nurse-led usual care.

A more detailed understanding of the components of the intervention which are successful while others fail to change behaviour requires gaining insight into the 'black box' of the intervention. Prospective recording is a method to evaluate the intervention process in terms of materials used, themes of communication, and time needed. Studying interactions by means of audiotaped recordings can assess the use of motivational interviewing and the principles of shared decision making. This information will be used to examine factors that moderate or mediate intervention effects. Since attitudes play an important role in adapting to a new way of working [39], it is important to evaluate the experiences of the general practitioners and practice nurses with the intervention, to determine the feasibility of a wider implementation of the intervention.

The patients in the intervention arm will probably notice the attempts to promote patient involvement and the changes in the relationship between health professional and patient and in the communication during the consultations. In an earlier community-oriented and individual-oriented prevention project for cardiovascular diseases in the Dutch province of Limburg, frictions and irritations were found among both health advisors and patients in the consultations [40]. In this project, the research agenda had determined a large part of the agenda setting of the prevention activities, and the options for risk reduction were limited to certain themes. In the context of CVD prevention, a deliberative model of the relationship between physician or practice nurse and patient is preferable to other models of the physician-patient relationship [41]. In this model, the aim of physician-patient interaction is to help the patient determine and choose the best health-related values that can be achieved in the clinical situation. The role of the physician is that of a teacher or a friend, engaging the patient in a dialogue on the best course of action. The IMPALA project will involve interviews in which patients will be asked about their experiences with and opinions about the IMPALA intervention, so that this can be evaluated from an ethical perspective.

We hypothesise that the intervention will modify patients' adherence to lifestyle advice, but the intervention may also improve the healthcare process implemented by GPs and practice nurses and hence the amount of time and effort required from the professionals [42]. Since this study will determine both the effects and the costs of the implementation of the nurse-led intervention an economic evaluation of the intervention is planned to compare the cost-effectiveness ratio in the intervention group with that in the control group.

### Research questions

1. What is the effect of our nurse-led intervention for CVRM, including risk communication, a decision aid and adapted motivational interviewing, on patients' adherence to lifestyle advice? [Effect evaluation]

2. To what extent do the nurses adhere to the intervention for CVRM and decision support, and what are the experiences and opinions of GPs and practice nurses about this strategy? [Process evaluation]

3. How do patients experience the nurse-led intervention for CVRM, and what is the ethical value of the intervention? [Ethical evaluation]

4. What is the incremental cost-effectiveness ratio of the nurse-led intervention for CVRM and decision support compared to usual care by a practice nurse? [Economic evaluation]

## Methods

### Design

The IMPALA study is a cluster-randomised controlled trial involving 20 general practices and 720 patients in the Netherlands. An independent statistician will perform a central block randomisation. Practices will be randomly allocated, 10 practices to the intervention group and 10 practices to the control group, after stratification into 4 geographical regions. Assessments will be made at the inclusion of the patients in the study, at 12 weeks and at 52 weeks. A flowchart of the study is shown in Figure 1.

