### Sample size calculation and feasibility of recruitment

The study will be powered on outcomes on patient behaviour to detect an absolute 52-week, post-intervention, between-group difference of 15% (50 – 65%) in patients' self reported adherence to life-style advice on smoking, diet, alcohol and physical exercise (alpha = 0.05, power = 0.80). The figure of 50% represents the average adherence by patients with chronic diseases [13]. The power calculation for clustered data analysis assumes an intra-class correlation coefficient (ICC) of 0.04. ICC values in earlier trials among general practitioners were 0.06 [44] and 0.03 [45]. Since we expect that the nurses will perform well in terms of adhering to the working protocol, we expect a lower ICC, with a maximum of 0.04. Thus, the within-cluster variance will be almost equal to the between-cluster variance. This implies that 600 patients are needed (300 per group) at 52 weeks. It is our intention that a total of 720 patients will be recruited by the GPs or practice nurses, to compensate for an expected 15% loss to follow-up (in an earlier trial by [name], 87% of the included patients responded at the 6-month follow-up [45]). It should be possible to prospectively recruit 720 patients (36 per practice) in 6 months, as Dutch general practices each have 100–150 of these patients, who visit the practice at least once a year for regular monitoring.

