### Data analysis

Since it is not possible to restrict our study to one primary outcome for all patients beforehand, the study will examine 6 different lifestyle changes: smoking, physical exercise, fat intake, fruit, vegetables and alcohol.

To assess the difference in primary outcomes between the arms, the arms will first be compared in terms of changes in the specific lifestyle issues, independent of the targets chosen by the intervention patients. We will use a T test for continuing variables and a χ^2 ^test for dichotomous variables.

A second analysis of primary outcomes is a multilevel regression analysis (using SPSS and MLwin), which uses adherence to the primary outcomes of lifestyle change as the dependent variables and group allocation and pre-intervention scores as independent variables. Additional independent variables will be included in the model, such as patient characteristics (age, sex, anxiety and risk of CVD). Additional regression analyses will focus on the effect at T2.

The third analysis involves constructing a simple standardised overall adherence score for the six lifestyle items, which expresses to what extent, on average, patients achieved the behaviour change goals of the national recommendations for a healthy lifestyle. The score of the intervention group will be compared with that of the control group.

Finally, the reduction in the 10-year risk of CVD will be analysed for differences between the two arms. The risk of CVD will be analysed with a multilevel regression analysis, which uses the risk at 52 weeks as the dependent variable and group allocation and pre-intervention risk as independent variables.

The secondary outcomes will also be analysed for the differences between the arms, using a T test for continuing variables and a χ^2 ^test for dichotomous variables. We also intend to use a multilevel regression analysis (using MLwin) which uses e.g. self-efficacy and attitudes at T1 as the dependent variables and group allocation and pre-intervention scores as independent variables. Additional independent variables, such as patient characteristics (age, gender, risk of CVD and socio-economic status), will also be included in the model. Additional regression analyses will focus on the effect at T2. Further analyses for subgroups of patients are also possible.

In addition, we will describe the personal targets of the patients in the intervention arm, which will be recorded by the nurses.

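### Practices are randomised within four regions, but no described analysis names region; if regions differ, the standard error of the arm effect is too large and the test is conservative

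*Protocol article*

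**What the plan says.** The Design section describes central block randomisation of 20 general practices, 10 to each arm, "after stratification into 4 geographical regions".

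The Data analysis section of the effect evaluation describes these between-arm analyses:

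- **First comparison of the primary outcomes, and comparison of the secondary outcomes:** t tests and chi-square tests, with no covariates.
- **Second analysis of the primary outcomes:** "a multilevel regression analysis (using SPSS and MLwin"), with "group allocation and pre-intervention scores as independent variables". Further variables will be added, introduced as examples: age, sex, anxiety and CVD risk.
- **Overall adherence score:** a comparison of the arms, with no model given.
- **10-year CVD risk:** a multilevel model with allocation and pre-intervention risk. No further covariates are mentioned.
- **Secondary outcomes, multilevel model:** allocation and pre-intervention scores, plus examples of further variables (age, gender, CVD risk, socio-economic status).

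Region appears in none of them. The section also names no estimator, reference distribution or degrees-of-freedom method for the multilevel models.

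**The concern.** Stratified allocation puts nearly equal numbers of practices per arm in each region, so regional differences largely cancel in the arm comparison. The analysis benefits only if region is in the model. Otherwise the regional differences still count as unexplained spread between practices, and the estimated standard error exceeds the true variability of the arm effect.

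The arm effect is judged against the variation among only 20 practices. Precision at that level is scarce, and stratification was a way to gain some. At stake are the width of the confidence interval and the power. There is no risk of excess false positives from this omission.

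**Working it through.** The plan gives no figure for regional variation, so there is no stated result on this point to reproduce. The check takes the plan's design inputs and varies the unknown share.

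**Inputs from the protocol article**
- 20 practices, 10 per arm, four regional strata (Design).
- ICC: the calculation "assumes an intra-class correlation coefficient (ICC) of 0.04".
- Patients analysed: 300 per arm at 52 weeks, so 600/20 = 30 per practice.
- Effect: 50% against 65%. Average variance (0.25 + 0.2275)/2 = 0.23875, standardised effect 0.15/√0.23875 = 0.307.
- "alpha = 0.05, power = 0.80", taken as two-sided.

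**Assumptions, not in the article**
- Strata of 6, 6, 4 and 4 practices, split equally between arms.
- Region holds a share *s* of the between-practice variance.
- Equal practice sizes, normal practice means, no baseline adjustment.
- A t reference in both analyses, so that only the region term differs.

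**Step 1. Variance of a practice mean**, in units of the patient-level variance: 0.04 + 0.96/30 = 0.072.

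**Step 2. True standard error of the arm difference.** With allocation balanced within region, regional variation cancels: SE = √[(2/10) × (0.072 − 0.04*s*)].

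**Step 3. Standard error reported when region is omitted.** The residual mean square on 18 df also picks up regional spread within each arm. With 3, 3, 2 and 2 practices per arm, the expected sum of squares per arm is 10 × (1 − 0.3² − 0.3² − 0.2² − 0.2²) = 7.4 times the region variance. Over both arms this is 14.8/18 = 0.822. So SE ≈ √[(2/10) × (0.072 − 0.04*s* + 0.822 × 0.04*s*)].

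**Step 4. Type I error and power**, by simulating practice means (200,000 runs per setting), with t on 18 df without region and 15 df with it.

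| *s* | True SE | SE, region omitted | Ratio | Type I, omitted | Type I, fitted | Power, omitted | Power, fitted |
|---|---|---|---|---|---|---|---|
| 0 | 0.120 | 0.120 | 1.00 | 5% | 5% | 68% | 67% |
| 0.2 | 0.113 | 0.119 | 1.05 | 4.1% | 5% | 69% | 72% |
| 0.3 | 0.110 | 0.118 | 1.08 | 3.7% | 5% | 70% | 74% |
| 0.5 | 0.102 | 0.117 | 1.15 | 2.9% | 5% | 72% | 80% |

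Strata of 2, 4, 6 and 8 practices give nearly the same type I error with region omitted: 4.2%, 3.8% and 3.0% at shares of 0.2, 0.3 and 0.5.

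**Why the starting power is 68% and not 80%.** This is a separate matter from region. The unclustered requirement is 170 per arm. With 30 per practice the design effect is 1 + 29 × 0.04 = 2.16, so 170 × 2.16 = 367.2, or 368 per arm and 736 in total, against the stated 600. At 600, power is about 72% with a normal reference and 68% on 18 df.

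**The case against.** **The covariate lists are open.** The primary and secondary multilevel models introduce their extra covariates by example, so region is unnamed rather than excluded. This stands. Only the CVD-risk model reads as a closed list, and even that may be a journal article's summary. Still, every example given is a patient characteristic, and the one factor that the randomisation used is missing throughout.

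**The error is on the safe side, and its size is assumed.** This stands too. The article gives neither the regional share nor the strata sizes, and the change in power from fitting region runs from −1 to +8 points depending on that share. The multilevel models adjust for baseline scores, and stable regional differences in lifestyle would show at baseline and be partly absorbed. The figures above probably overstate the gain under the planned models. Several outcomes are also proportions, for which normal practice means are an approximation.

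**Stronger readings that the article does not support.** A reader might infer that leaving out region inflates the false-positive rate. The table shows the opposite.

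A reader might also infer that, with 20 practices, the plan commits to maximum likelihood with a normal reference, which would give about 7.9% type I error (6.6% for restricted maximum likelihood with a normal reference). The article names software but no estimator or reference distribution. It is compatible with restricted maximum likelihood and a t reference, which holds 5%. A condensed article commonly leaves this detail to the full plan, so silence here is not an error. It also acts in the opposite direction to the region omission, so the two should not be merged into one claim about standard errors.

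**Conclusion.** The point holds in limited form. The trial stratifies its practices by region and describes no analysis that names region. If regions differ after baseline adjustment, the reported standard error is too large: by about 5 to 15% when region holds 20 to 50% of the between-practice variance, under the assumptions listed. The test is then conservative, and about 3 to 8 points of power are forgone. If region explains nothing, nothing is lost by leaving it out.

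This concerns precision and consistency between design and analysis. It does not invalidate the trial's inference. It deserves correction because the remedy is cheap and the number of practices is small.

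**What to change.** State that the multilevel models for the primary, secondary and CVD-risk outcomes include region (four categories, fixed effect) alongside allocation and the baseline value. The CVD-risk model needs the explicit addition most, because its list is closed. If region is to be left out, say why.

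Cost: one sentence, 3 of the 18 between-practice degrees of freedom, and about 1 point of power (68% to 67%) if region explains nothing.

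As accompanying advice, not as the correction of an error, the same sentence could name restricted maximum likelihood and a small-sample t reference (about 15 df once region is fitted). The two belong together: with region fitted and 15 df, a normal reference would give about 6.9% type I error even with restricted maximum likelihood.
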